### Statistical analyses

We will assess intervention group equivalence on baseline and outcome variables using relevant univariate tests (chi-square and Kruskal-Wallis) with statistical significance set at *p* < 0.05. Descriptive statistics (percentages, frequencies, means, standard deviations, and 95% confidence intervals) will be used to summarize the results at each timepoint and determine feasibility and acceptability. For feasibility, successful retention is defined as at least 70% of enrolled participants completing the intervention sessions and monthly follow-ups. Acceptability is defined as at least 70% of participants reporting high average ratings (≥ 7 of 10) on acceptability and satisfaction measures. In order to address the secondary objective examining the plausibility of clinical improvement, we will calculate the proportion of participants who report a “moderately important” pain reduction of 30% or greater for each intervention group using the ratings of average pain intensity over the past week. We also plan to explore potential covariates and predictors of treatment response (e.g., age, sex, QST).

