The purpose of the current pilot study is to evaluate whether it is feasible to conduct a clinical trial investigating CCBR for adults with cLBP in preparation for a subsequent, adequately powered randomized controlled trial (RCT) [98–101]. The primary objective is to test the feasibility and acceptability of 5 days of CCBR practice delivered via standardized audio recordings, compared to a structurally equivalent deep breathing sham control intervention [102–104], in a sample of 24 adults with cLBP. We expect it to be feasible to recruit, retain, and randomize participants to the intervention groups and expect at least 70% of participants to rate the interventions as acceptable and satisfying (≥ 7 out of 10). The secondary objective is to gather data regarding the plausibility that the CCBR intervention can result in clinically meaningful improvements in pain and pain-related variables [100, 105]. To demonstrate plausibility of improvement, we expect a greater ratio of participants in the CCBR group, compared to the control group, will meet the clinically significant treatment response target of ≥ 30% improvement in pre-post average pain intensity ratings [106–108]. A 30% reduction in pain is considered a moderately important change following treatment and is commonly used to determine clinical significance and/or treatment response in pain RCTs [107–111]. Results from this study will not be used to make claims about preliminary efficacy or to determine power for future sample size calculations [98, 100, 112] but rather to provide feasibility estimates, refine the interventions, and inform the successful design and implementation of an anticipated RCT, which will rigorously test the efficacy and mechanisms of this self-management breathing practice for adults with cLBP.

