Although there are several strengths to the proposed study, such as the multimethod assessments, standardized interventions, and a randomized controlled design, there are limitations to highlight. Considering this pilot RCT is a smaller version of a future efficacy trial, the current “dose” of a 5-day CCBR practice may be insufficient for clinically meaningful changes in the proposed primary efficacy outcomes of pain intensity and pain interference. It may be that this self-management practice needs to be maintained over a longer period of time for substantial or sustained benefits. For example, clinical trials of breathing exercises typically involve daily practice for at least 4 weeks and often up to 8 or 12 weeks [24, 25, 185]. Moreover, while we can visually monitor treatment fidelity during the in-person BAT sessions, we will be unable to determine fidelity when participants practice the interventions at-home. Additionally, there may be unknown safety issues with the CCBR intervention (e.g., cyclic hyperventilation, breath holding, mindful body awareness) that are over- or under-represented in the small sample size of the current study. We will monitor adverse events by soliciting expected and unexpected side-effects of the intervention, but, ultimately, a larger study is needed to establish the safety of the intervention. Finally, we caution overinterpretation of the results regarding the plausibility of improvement in pain-related outcomes. These analyses are considered exploratory to discern whether the intervention has any effects at all by providing initial evidence that the target of clinical significance (≥ 30% improvement in pain intensity), rather than statistical significance, is achievable for some people [100, 105, 106, 132]. If the ratio of participants showing meaningful improvement favors the control, we may need to modify the sham control intervention or consider a three-arm trial design for the larger follow-up trial [182].

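### Difference tests at p < 0.05 are used to assess group equivalence on baseline and outcome variables, which about 12 completers per arm cannot support

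*Protocol article*

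**What the plan says.** The Statistical analyses section of the protocol article opens with a rule for judging whether the arms are alike, namely "equivalence on baseline and outcome variables using relevant univariate tests". The two tests named are Kruskal-Wallis and chi-square. The threshold is given as follows: "with statistical significance set at *p* < 0.05". The rule names no equivalence margin, and it does not say which outcome variables are meant or when they are compared.

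The next sentence turns to description: "Descriptive statistics (percentages, frequencies, means, standard deviations, and 95% confidence intervals) will be used to summarize the results at each timepoint". The secondary objective is then handled by giving the proportion in each arm with at least a 30% pain reduction.

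Two other statements bear on the rule:

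- Background, last paragraph: "Results from this study will not be used to make claims about preliminary efficacy or to determine power for future sample size calculations".
- Discussion, limitations paragraph: the analyses of improvement in pain-related outcomes are exploratory and ask whether the clinical target ("≥ 30% improvement in pain intensity), rather than statistical significance, is achievable for some people").

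The Participants section adds that no power analysis was done.

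**The concern.** There are two problems, and the first does not depend on how the sentence is read.

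**Equivalence from a difference test.** Chi-square and Kruskal-Wallis tests take no difference as the null hypothesis. Failing to reject it in a small sample is weak evidence of anything. A rule that sets out to assess equivalence and offers only a p < 0.05 threshold invites readers to take p > 0.05 as showing that the arms are alike. This matters because the Discussion expects the two arms to be equivalent on engagement, credibility and expectation of benefit. The same section warns that a demanding control raises the type II error and that small effects may cause a promising intervention to be dropped too early.

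**Testing outcomes between arms.** Outcome variables stand beside baseline variables as a second category, so the plain reading is that outcomes after randomisation are tested too. The article gives no other purpose for such tests, and they fit poorly with a pilot that disclaims preliminary efficacy. The Discussion says the pilot will be used to optimise the interventions and adjust the design of the next trial. Chance findings and low-power null results could both influence those decisions.

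**Working it through.** **1. Sample size.** The Participants section plans 24 completers with 20% attrition: 24 / (1 − 0.20) = 30, which reproduces the stated recruitment target. With 1:1 allocation (Study design), 24 completers give about 12 per arm.

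**2. What a non-significant result can show at 12 per arm.** The Kruskal-Wallis test was simulated with normal data, 5,000 runs per setting, at p < 0.05:

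| True difference | Chance of p < 0.05 | Chance of p > 0.05 |
|---|---|---|
| 0 | about 5% | about 95% |
| 0.5 SD | about 22% | about 78% |
| 0.8 SD | about 46% | about 54% |

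For a binary variable, taking 50% against 25% as an assumed example, power is about 24% by the usual two-proportion formula.

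The width of the confidence interval gives the same message. The half-width of a 95% interval for a difference in means, in SD units, is t × √(2/n):

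- 12 per arm (22 df): 2.074 × √(2/12) = 2.074 × 0.408 = 0.85 SD.
- 15 per arm, if all 30 were randomised and analysed (28 df): 2.048 × √(2/15) = 2.048 × 0.365 = 0.75 SD.

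Even an observed difference of exactly zero would leave true differences of about 0.75 to 0.85 SD inside the interval.

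**3. Chance findings if outcomes after randomisation are tested.** The article states no number of tests, so the following are counts made from Table 2 and the measurement sections, with one score per scale.

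- *Visit 3 only.* Questionnaires: five PROMIS forms plus nine others = 14. Physical, sensory and physiological: Back Performance Scale, movement-evoked pain and physical performance battery (3); pressure threshold, temporal summation at two sites and conditioned pain modulation (4); heart rate variability (5); oxygen saturation (1); systolic and diastolic pressure (2) = 15. Total 14 + 15 = 29.
- *Visit 3 and the monthly surveys.* Questionnaires: PROMIS 5 × 4 = 20; four instruments at four time points = 16; five instruments at three time points = 15; sum 51. Total 51 + 15 = 66.
- *Physiology also split by epoch and visit.* At Visit 3: 51 + 3 + 4 + (6 × 3) + (2 × 2) = 80. Adding Visit 2 during and after the practice: 80 + (6 × 2) + 2 = 94.

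With no true effect anywhere, the expected number of results below 0.05 is 0.05 × k:

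- k = 29: 1.45
- k = 66: 3.3
- k = 94: 4.7

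These expectations do not depend on correlation between outcomes. The chance of at least one such result does. At k = 66 it is 1 − 0.95^66 = 97% if the tests were independent, and by simulation about 87%, 68% and 44% at a common correlation of 0.3, 0.5 and 0.7.

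**4. If only baseline values were meant.** Step 3 and the tension with the efficacy statement both fall away. What remains is significance testing of baseline balance after randomisation, where any difference is due to chance by design, and step 2 still applies.

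**The case against.** The best case for the plan has four parts.

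- **The sentence may not mean post-randomisation efficacy outcomes.** It names no time points, and the next sentence assigns the results at each time point to descriptive statistics. It may mean outcome measures at baseline, or the feasibility and acceptability outcomes on which the arms are expected to be alike. This stands as a point about ambiguity. It does not rescue the rule, because a difference test fails to show equivalence under any of these readings. It does affect the remedy: between-arm comparison of acceptability, adherence and expectancy is useful and should be kept as estimates.
- **There is no flat contradiction.** A reader might infer that the plan forbids what it then prescribes. The Background statement limits the claims to be made and does not prohibit tests. The Discussion statement concerns improvement in pain outcomes only, and the responder proportions by arm are consistent with it. Tension is the right word.
- **Absent multiplicity control is not a fault here.** A reader might infer some 66 uncontrolled tests and a near-certain false positive. The article gives no count, 97% needs independence that overlapping pain and distress scales will not have, and an exploratory pilot may leave such matters to an analysis plan that is not shown. The chance-finding figures indicate how p-values from this rule should be read; they do not show an omission.
- **Harm is partly forestalled.** Pain intensity and pain interference are already named as primary outcomes for the later trial, and the Discussion cautions against overinterpretation. This lowers the stakes but leaves the rule in the text.

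It is also true that unadjusted 95% intervals would exclude zero by chance as often as the tests would fall below 0.05. The gain from intervals is that they show the imprecision and cannot easily be mistaken for evidence of equivalence.

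**Conclusion.** The point holds as a badly fixed rule. The stated method cannot deliver the stated inference: at about 12 per arm, a true difference of 0.5 SD would give p > 0.05 about 78% of the time, and one of 0.8 SD about 54% of the time. These figures assume normal data, equal arms and 24 completers.

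On the plain reading, the rule also adds between-arm outcome testing that sits badly with the pilot's stated purpose, with roughly 1.5 to 5 results below 0.05 expected by chance. That range rests on one score per scale and on which time points and epochs are tested, none of which the article fixes. On the baseline-only reading, this second part does not apply.

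The feasibility and acceptability criteria and the 30% responder proportions are unaffected.

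**What to change.** Remove the p < 0.05 equivalence rule from the opening sentence of Statistical analyses and replace it with wording to this effect:

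> Baseline variables will be described by arm without significance tests. Outcomes, including acceptability, adherence and treatment expectancy, will be reported as between-arm differences with 95% confidence intervals, labelled exploratory. An interval that includes zero will not be read as equivalence, and one that excludes zero will not be read as efficacy. Statistical significance in this pilot will not be used to select or drop outcomes for the later trial.

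If the sentence was meant to cover only baseline values of the outcome measures, say so explicitly; the change to baseline description without tests still applies.

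Cost: a wording change and a few extra intervals. The article already plans 95% confidence intervals as descriptive summaries but does not say they will be given for between-arm differences, so that part is an addition. Data collection and trial conduct do not change.

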### Procedure

Interested participants will complete a telephone screening to determine initial eligibility, and those who qualify will be scheduled for their first visit at the University of Florida Pain Clinical Research Unit to obtain informed consent and complete several baseline assessments and physical functioning tasks. At the end of Visit 1, participants will be scheduled for two additional study visits to occur within a 1-week period (pre-intervention and post-intervention). Participants will also be asked to complete two additional baseline surveys online using REDCap between Visit 1 and Visit 2, which is intended to reduce the participant burden and length of Visit 1. At Visit 2 (pre-intervention), participants will be randomized to the Standard- or Focused-BAT intervention before undergoing quantitative sensory testing procedures. Then, participants will be instructed via an audio-recording to practice their assigned breathing intervention for the first time with the researcher. Physiological data will be collected before, during, and after the breathing practice at both Visit 2 and Visit 3. Following Visit 2, participants will receive an email to practice BAT first thing in the morning if possible by following along to the recording on their own at home. If not possible to practice upon awakening, participants will be asked to practice at least 2 h after a meal. We will attempt to schedule intervention sessions over five consecutive days when possible (Monday–Friday). When not possible, we will require that the last at-home session and last in-person session (BAT sessions 4 and 5) be practiced on consecutive days. At Visit 3, participants will practice their assigned breathing intervention for the 5th and final time and then complete post-intervention questionnaires, quantitative sensory testing procedures, and physical functioning tasks. Finally, participants will be asked to complete 1-, 2-, and 3-month follow-up surveys online using REDCap.

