#### Baseline assessment and secondary outcomes

Consistent with the purpose of pilot RCTs [100, 117], the additional measures reflect baseline, outcome, and possible process variables that we anticipate will be included in a subsequent efficacy trial [132]. Table 2 indicates the schedule for collecting these psychometrically sound measures, and Additional file 1: Appendix 2 includes more detailed descriptions. The baseline assessment will include demographic and pain and health history questions that align with items recommended by the NIH Task Force on Research Standards for cLBP and the Back Pain Consortium (BACPAC) minimum dataset [119]. Moreover, many of the biobehavioral and patient-reported measures of this study were selected to be consistent with BACPAC recommendations to (1) assess meaningful outcomes following an intervention and (2) include phenotyping measures that may predict who responds to an intervention [158]. Although considered secondary outcomes in the current study, the primary clinical pain outcome measures for a future efficacy trial will be pain intensity and pain interference. The NIH PROMIS pain intensity-short form scale [133] will be used in analyses to determine clinical significance for the proposed study and subsequent efficacy trial by assessing improvements over the last 7 days on average using an 11-point NRS (0 = no pain, 10 = most pain imaginable). Finally, participants will also complete behavioral and physiological assessments at pre- and post-intervention, including physical functioning tasks, quantitative sensory testing, and heart rate variability.

**Table 2 Tab2:** Timeline of study assessments and measures

*Timepoint*	Baseline		Pre-intervention	Post-intervention	Follow-ups		
Variable, category, or measure	Screening	Visit 1	Visit 2	Visit 3	1 months	2 months	3 months
Demographic information	X	X					
Contact information	X						
Eligibility criteria	X	X					
Health history	X	X					
Pain history [119]	X	X					
NIH PROMIS Positive Affect and Well-being [133]		X					
Stress and Adversity Inventory^a^ [134]		X					
Feasibility and acceptability							
Treatment acceptability				X			
Treatment expectations [135]			X				
Blinding effectiveness				X			
Adverse events			X	X			
Secondary outcomes and process measures							
NIH PROMIS-Short forms (pain intensity, pain interference, depression, sleep disturbance, sleep-related impairment) [133, 136–138]		X		X	X	X	X
Brief Pain Inventory-Short form [139, 140]		X		X	X	X	X

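### The Visit 3 pain-responder rating looks back 7 days, so on the preferred schedule up to 3 of its days fall before the first session

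*Protocol article*

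**What the plan says.** The last paragraph of the Background sets the responder target as at least 30% "improvement in pre-post average pain intensity ratings". The Statistical analyses section repeats the 30% threshold and calculates the proportion in each arm "using the ratings of average pain intensity over the past week". The section on baseline assessment and secondary outcomes names the instrument, the PROMIS pain intensity short form, which determines clinical significance "by assessing improvements over the last 7 days on average using an 11-point NRS". Table 2 schedules it at Visit 1, at Visit 3 and at months 1, 2 and 3, but not at Visit 2.

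The Procedure section fixes the timing. At Visit 2, "participants will be instructed via an audio-recording to practice their assigned breathing intervention for the first time with the researcher". At Visit 3, "participants will practice their assigned breathing intervention for the 5th and final time and then complete post-intervention questionnaires". On spacing it says "We will attempt to schedule intervention sessions over five consecutive days when possible" and gives Monday to Friday as the pattern. Visits 2 and 3 are to fall inside one week. Under Physiological assessments, the aim is to hold both visits at the same time of day.

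The Discussion calls the responder analysis exploratory and warns that five days of practice may be too short. It does not mention that the recall period reaches back before treatment.

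**The concern.** A pre-post comparison needs a post rating that describes the period after treatment began. Here the recall period is longer than the treated period on the schedule the trial prefers, so the Visit 3 score can mix untreated and treated days. A participant whose pain fell by the target amount once practice started could then be counted as a non-responder. Two participants with the same benefit could also be classified differently because their visits were spaced differently.

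The protocol uses this outcome to learn whether the clinical target can be reached by some participants. The Discussion adds that, if the responder ratio points towards the control, the sham may be modified or a three-arm design considered. With 24 completers, about 12 per arm, a few reclassified participants can change that ratio. A low responder count might also be put down to the short intervention, which the Discussion names as a limitation, when the measurement window had contributed.

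**Working it through.** The protocol gives no expected responder rate and no power calculation, so there is no planned figure for this outcome to reproduce. Its one sample-size figure does reproduce: 24 / (1 − 0.20) = 30. It plays no part below.

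**Inputs from the protocol**
- Recall period: 7 days = 168 hours (Baseline assessment and secondary outcomes).
- Session 1 at Visit 2, post rating at Visit 3 after session 5 (Procedure).
- Preferred spacing: Monday to Friday (Procedure) at the same time of day (Physiological assessments), so 4 × 24 = 96 hours.
- Longest spacing: about one week (Procedure).
- Responder threshold: 30%.

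**Overlap on the preferred schedule**
168 − 96 = 72 hours, or 3 of 7 days before session 1. If the day of Visit 3 is instead counted as a whole treated day, 5 of the 7 days are treated and 2 precede treatment.

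**Effect on the recorded reduction**
Assume (not in the protocol) that pain stays at its baseline level B until session 1, falls at once by a fraction r, and is averaged evenly over the week. With d treated days in the window:

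recorded mean = B × [(7 − d) + d(1 − r)] / 7 = B × (1 − r × d/7)

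The recorded reduction is therefore r × d/7, and the reduction needed to record 30% is 0.30 / (d/7).

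| Treated days d | Untreated days | Recorded if r = 30% | r needed to record 30% |
|---|---|---|---|
| 4 | 3 | 17.1% | 52.5% |
| 5 | 2 | 21.4% | 42.0% |
| 6 | 1 | 25.7% | 35.0% |
| 7 | 0 | 30.0% | 30.0% |

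The first two rows are the preferred schedule under the two ways of counting days. An effect that builds up over the week would need to be larger still.

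**Example on the 0–10 scale**
A participant entering at 4, the eligibility minimum, has pain of 2 on every treated day. With 3 untreated days the average is (3 × 4 + 4 × 2) / 7 = 20/7 = 2.9. Reported as 3, that is a 25% reduction and a non-response, although pain on treated days has halved.

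**Effect on the responder proportion**
As a further assumption, let individual on-treatment reductions be normal with mean 30% and SD 20 to 30 percentage points, so that 50% truly reach the threshold.
- 3 untreated days: 1 − Φ((0.525 − 0.30)/0.20) = 13.0% and 1 − Φ((0.525 − 0.30)/0.30) = 22.7%.
- 2 untreated days: 1 − Φ((0.42 − 0.30)/0.20) = 27.4% and 1 − Φ((0.42 − 0.30)/0.30) = 34.5%.

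With a mean of 40%, the true share is 63% to 69% and the recorded share with 3 untreated days is 27% to 34%.

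**Later ratings**
Even if the month is counted from session 1 and taken as 30 days, the 7-day window of the 1-month rating opens at about day 30 − 7 = 23, well after treatment began. It contains no pre-treatment days.

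**The case against.** The primary outcomes are feasibility and acceptability. The protocol disclaims any use of the results for efficacy claims or for powering the next trial, and it warns against overinterpreting this analysis. If the aim is only to show that the target is achievable, dilution makes the test conservative, and a participant still recorded as a responder remains credible. The 7-day rating matches the entry criterion, which also refers to the past week, and it is the measure planned for the efficacy trial, so rehearsing it is a proper purpose of a pilot. All of this stands, and it limits how serious the point can be.

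A reader might infer more than the documents support:
- *That response is understated as a matter of fact.* This needs a real on-treatment improvement and even averaging over the week. Recall weighted to recent days would shrink the dilution, and regression to the mean after entry at pain of 4 or more could push the recorded responder proportion the other way.
- *That the comparison is biased towards one arm.* Both arms follow the same schedule and instrument. Dilution lowers both proportions and tends to narrow the gap between them, but it does not by itself favour either.
- *That the trial has no other view of pain.* PROMIS intensity is the only rating named for the responder count. Table 2 also has the Brief Pain Inventory and global impression of change at Visit 3 and follow-up. The Back Performance Scale gives movement-evoked pain at Visits 1 and 3, rated straight after each task with no recall period.
- *That the responder should be redefined on a 24-hour rating.* Such a rating is noisier and has no entry floor, so some participants could start near zero, where a 30% reduction means little. It would also depart from the measure planned for the next trial.

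What the objection does not answer is that the overlap arises on the schedule the trial prefers, that the Background fixes the target as pre-post, and that the overlap is nowhere acknowledged.

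**Conclusion.** The timing conflict holds. The instrument, recall period, visit schedule and pre-post definition are all fixed in this document. Together they place up to 3 of the 7 recalled post days before session 1, falling to none if Visits 2 and 3 are a full week apart.

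The consequence is conditional. Given an on-treatment improvement and even recall, the Visit 3 responder proportion is diluted in both arms. The figures of 17% to 21% recorded and 42% to 52.5% required illustrate the preferred schedule under immediate onset. They are not estimates, and the true size cannot be fixed from the documents.

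This is a moderate issue in an exploratory, descriptive secondary outcome. It leaves the primary feasibility and acceptability outcomes untouched. It deserves correction because the Discussion attaches a possible redesign of the control to the responder ratio.

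**What to change.** - Keep the 7-day PROMIS 30% responder at Visit 3 as planned.
- Pre-specify and report, by arm, the 30% responder proportion from Visit 1 to the 1-month rating. The data are already in Table 2, so no new collection is needed.
- State, wherever the Visit 3 result is interpreted, that its recall period can include up to 3 days before session 1.
- Optionally, and only as a supplement, add one average-pain item with 24-hour recall at Visit 2 before session 1 and again at Visit 3. Sessions 4 and 5 must fall on consecutive days, so the Visit 3 window would lie within the treated period.

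The cost is one extra tabulation and a sentence of interpretation, plus one questionnaire item at two existing visits if the option is taken. The 1-month rating answers a somewhat different question, since it reflects a later effect and is exposed to loss to follow-up. The 24-hour item is noisier and has no entry floor, so it should not replace the planned definition.
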